**3.6 Sample Size Estimation**

The minimum sample size required to test the study hypotheses was calculated using the two proportions formula (Lemeshow, Hosmer, Klar, & Lwanga, 1990). The formula gave the required number (n) for each group.

2

{√2p̌ (1 − p̌) + Z1−β√p1(1 − p1) + p2(1 − p2)}

n =

(p1 − p2)2

Parameters from different intervention studies were substituted into the formula to calculate sample size as shown in Appendix H. However, a study among students by Mohammed et al. (2016) was adopted to calculate the sample size for this study.

P1 = 0.032 (proportion of students who initiated smoking among students in the intervention group after six months intervention.

P2 = 0.088 (proportion of students who initiated smoking among students in the control group after six months.

P = proportion of all subjects receiving smoking intervention after six months ((P1 +

P2)/2).

P = (0.032 + 0.088)/2 = 0.06

With Z1-α/2 = 1.96 at 95% CI and Z1-β = 1.28, at 90% power gave a minimum sample

size (n0) of 281

Adjustments were made for estimated response rates (Aday & Cornelius, 2006) thus:

i) Adjustment for estimated response rate, where the estimated attrition rate

is 20% = 337.2

This gave a sample size of 337.2 students in each group. Cluster randomized control trials are measured by design effect given as (1+ (M-1) X ICC) = 1.085.

ICC – Intra Cluster Correlation = 0.01

M – Average Cluster Size

337.2 x 1.085 (effect size of cluster random sampling) = 365.9

This gave a sample size of 366 students per group, which was then multiplied by two since the study is in two arms. Therefore, 732 is the sample required for this study.

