**3.7.1 Sequence Generation**

A biostatistician who will not be involved in the trial will generate the allocation sequence. Using a block randomization (1:1 ratio) of two digit blocks A and B (each containing one intervention and one control, to ensure equal distributions in the two groups will be used), two schools each will be allocated to intervention and control groups.

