**3.11 Intervention**

At this stage permissions and consent would had been sought from the Ministry of Education, District Directors of Education, Chairmen of the Parent Teacher Associations, parents/guardians, and students to carry out the study. All materials for the study will be ready at this stage. The objectives of the study and the eligibility criteria to participate in this study will be explained to all the students’ involved. Students will go through medical check-up which will be carried out by the two clinicians in order to pass eligibility criteria to be enrolled into the study.

The self-administered questionnaire will be given to students to complete. Health staff will measure students anthropometric and blood pressure measurements. Confidentiality and anonymity will be assured at all stages of the study. The module will be implemented in the intervention schools for a period of six months but not in the control schools. Then at the end of six months the same questionnaire will be given to students in both the intervention and the control schools. Health staff who will not take part during the baseline data collection will take anthropometric and blood pressure measurements of students at post intervention study. A total of 848 students will participate in the study; intervention (424) and the control (424) schools. Contamination of the intervention will be prevented by having intervention and control schools with distances between them.

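### The design effect of 1.085 implies clusters of 9.5 students, but the trial has four schools of about 212; at the protocol's own ICC, 90% power is out of reach.

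*Protocol*

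**What the plan says.** Section 3.6 sizes the trial on smoking initiation at six months. Its inputs are "P1 = 0.032 (proportion of students who initiated smoking among students in the intervention group after six months intervention" and "P2 = 0.088 (proportion of students who initiated smoking among students in the control group after six months", and it continues "With Z1-α/2 = 1.96 at 95% CI and Z1-β = 1.28, at 90% power gave a minimum sample" size of 281 per arm. That figure is raised by 20% for attrition to 337.2. Clustering follows: "Cluster randomized control trials are measured by design effect given as (1+ (M-1) X ICC) = 1.085", with "ICC – Intra Cluster Correlation = 0.01" and M described only as the average cluster size, without a value. Multiplying by 1.085 gives 366 per arm and the conclusion "Therefore, 732 is the sample required for this study".

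Other sections fix what a cluster is and how many there are. Section 3.5.2 treats each school as a cluster, and section 3.7 makes the school the unit of randomization. Section 3.2 has four public secondary schools, and in section 3.7.1 "two schools each will be allocated to intervention and control groups". Section 3.11 sets enrolment: "A total of 848 students will participate in the study; intervention (424) and the control (424) schools".

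**The concern.** A design effect of 1.085 is a correction of under 10%. That is small for a trial that randomizes four schools with a couple of hundred students in each. If the correction uses the wrong cluster size, the sample size and the power in section 3.6 do not describe this design.

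Smoking is one of the listed primary outcomes and the only one on which the sample size rests. If the real power is far below 90%, a null smoking result would be read as evidence from a well-powered trial when it says little either way. With two clusters per arm there is also a limit on what recruiting more students can achieve, so the error may not be repairable by enrolment.

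**Working it through.** **Inputs.** From section 3.6: 3.2% and 8.8%, mean 6%; Z = 1.96 and 1.28; ICC 0.01; n0 = 281; attrition 20%; design effect 1.085. From sections 3.7.1 and 3.11: two schools per arm and 424 students per arm. School sizes are taken as equal, since only totals are given.

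**The protocol's own chain**
- 281 × 1.2 = 337.2; 337.2 × 1.085 = 365.9, i.e. 366 per arm; 366 × 2 = 732. These steps reproduce.
- The starting figure of 281 does not. The pooled two-proportion formula is n = [1.96·√(2 × 0.06 × 0.94) + Z·√(0.032 × 0.968 + 0.088 × 0.912)]² / 0.056².
- Z = 1.28 gives (0.6583 + 0.4269)² / 0.003136 = 375.5, so 376 per arm.
- Z = 0.84 gives (0.6583 + 0.2802)² / 0.003136 = 280.8. So 281 is the 80%-power figure.

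**Cluster size implied by 1.085**
- 1.085 = 1 + (M − 1) × 0.01, so M = 0.085/0.01 + 1 = 9.5.
- Clusters of that size would mean 732/9.5 ≈ 77 clusters, against four.

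**Design effect for the trial as planned**
- 848 students: M = 848/4 = 212; 1 + 211 × 0.01 = 3.11.
- 732 students: M = 732/4 = 183; 1 + 182 × 0.01 = 2.82.
- 848 less 20%: M = 169.6; 1 + 168.6 × 0.01 = 2.69.

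**Effective size and power for 3.2% versus 8.8%.** Effective n per arm is n divided by the design effect. Power comes from the same pooled formula. The last column uses a noncentral t with 4 − 2 = 2 degrees of freedom.

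| Case | n per arm | Design effect | Effective n | Power, normal | Power, 2 df |
|---|---|---|---|---|---|
| 732 | 366 | 2.82 | 129.8 | 48% | 21% |
| 848 | 424 | 3.11 | 136.3 | 49% | 21% |
| 848 less 20% | 339.2 | 2.69 | 126.3 | 47% | 20% |
| Unlimited students | – | – | 200 | 66% | 28% |

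**Ceiling.** With k schools per arm and m students per school, effective n = km / [1 + (m − 1) × ICC]. As m grows this tends to k/ICC = 2/0.01 = 200 per arm. That is below both 281 and 376.

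**Sensitivity to the ICC** (212 per school, no attrition, normal approximation)

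| ICC | Design effect | Power |
|---|---|---|
| 0.0005 | 1.11 | 91% |
| 0.001 | 1.21 | 88% |
| 0.002 | 1.42 | 82% |
| 0.005 | 2.06 | 67% |
| 0.01 | 3.11 | 49% |
| 0.02 | 5.22 | 32% |
| 0.05 | 11.55 | 17% |

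To keep 1.085 at 212 per school, the ICC would have to be 0.085/211 ≈ 0.0004.

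**Detectable difference at ICC 0.01.** At effective n 136, 3.2% versus 12% gives 79% power and versus 12.5% gives 82%. At 126, versus 12.5% gives 79% and versus 13% gives 82%. These are normal approximations; on 2 df, power over the same range is about 33% to 39%.

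**The case against.** The strongest objection is that M is never stated, so the contradiction is certain but its source is not. The ICC could be the misprint: 0.001 with M = 86 also gives 1.085, and at 0.001 with 212 per school power would be about 88%. Section 3.6 also refers to an Appendix H, which is not in the available text. This is a fair reason to ask for M to be stated and the ICC justified. It does not rescue the figure, because 0.01 is the only ICC printed, and even M = 86 does not describe four schools of 212 or 183.

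A second objection is that clustering is not the whole cause. This stands: 281 gives 80% power, so the 90% claim fails before clustering is considered. Clustering takes power from about 80% to about 50%. That makes the stated 90% less tenable.

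Third, the 2 df figure depends on the analysis. The protocol plans a generalized linear mixed model on baseline and follow-up data and sets no degrees of freedom, and all the power figures here rest on a simple comparison at six months. Baseline adjustment could change them. They do, however, use the comparison on which the protocol sized the trial, and section 3.2 names schools as the unit of analysis.

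Finally, enrolling 848 when the calculated minimum is 732 is not an error in itself. No derivation of 848 is given, but the extra students barely matter: power is 49% at 848 against 48% at 732. The calculation also says nothing about the continuous primary outcomes.

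**Conclusion.** The concern holds. Section 3.6 contradicts the trial's own design: its formula and ICC give a design effect of 3.11 for four schools of about 212, almost three times the stated 1.085. Power for the sizing difference is about 50% (47% after the planned loss), or about 20% on 2 degrees of freedom, not 90%. At ICC 0.01 the effective size is capped at 200 per arm and power at about 66%, so no number of students in these four schools reaches the claim.

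This rests on the protocol's ICC and event rates, equal school sizes (unequal sizes would lower power further) and a comparison at six months. Under the normal approximation, power near 90% would need an ICC of about 0.0005 and no attrition, and the protocol offers no support for such a value. This must be corrected.

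**What to change.** In section 3.6:

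- State M and replace 1.085 with 1 + (212 − 1) × 0.01 = 3.11. Justify the ICC.
- Delete the claims of 90% power and that 732 is the required sample. Correct the base figure too: 281 corresponds to 80% power, and Z = 1.28 gives 376.
- Do not simply put 3.11 into the existing chain. It gives 337.2 × 3.11 ≈ 1,049 per arm, which conflicts with the planned 848 and still fails, because M grows with the total. Present the design as fixed at four schools and 848 students.
- State what that delivers: about 50% power for 3.2% versus 8.8% (about 20% on 2 df), or about 80% by the normal approximation only for roughly 3.2% versus 12–13%. Say that the latter is also well below 80% on 2 df.
- Show a range of ICCs on both sides of 0.01, with attrition included.
- Present the smoking result as an estimate with a cluster-valid confidence interval, not as a powered test.

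The cost is a rewrite of section 3.6. No students or schools are added; section 3.1 says that all public secondary schools in the two districts are already included. The price is a less favourable power statement.

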**3.7 Randomization**

Randomization technique in the ratio 1:1 for intervention and control groups respectively will be carried out. Public secondary schools (clusters) will be the unit of randomization. Schools (students) will be randomly assigned to either the intervention or control group of the study on the same day participants will be selected for this study. It will however be performed after baseline data has been collected.

**3.7.1 Sequence Generation**

A biostatistician who will not be involved in the trial will generate the allocation sequence. Using a block randomization (1:1 ratio) of two digit blocks A and B (each containing one intervention and one control, to ensure equal distributions in the two groups will be used), two schools each will be allocated to intervention and control groups.

**3.7.2 Allocation Concealment Mechanism**

Allocation concealment will be achieved with sequentially numbered opaque sealed envelopes by an education officer containing treatment allocation cards (intervention and control). The envelopes will then be serially numbered from the outside.

**3.7.3 I**m**plementation**

An education officer who knows nothing about the research and not affiliated to any of the schools will be responsible for opening the envelopes in sequence and assigned schools to the groups. A second education officer will then document the group to which each school belong on a piece of paper and announce again to the school representatives.

**3.8 Blinding**

This study is single-blinded. Health staff who will take measurements of students’ anthropometry and blood pressure measurements will be blinded to participants groups and will not take anthropometry and blood pressure measurements at the post-test intervention. Researchers and physical education health instructor who that will facilitate the health education and the physical activity modules respectively will not be blinded as such. Contamination of the study will be minimized since there will be intervention and control schools and that schools are far apart each other.

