**3.5.2 Sampling Method**

Duration of time of recruitment to first follow-up visit in the study will be one month (four weeks), therefore participants will be recruited within a period of four weeks using the sampling frame (list of all secondary schools within the selected area). Systematic random sampling technique will be used to select students into the study from the list of sampling frame given by headmasters of the schools. Using table of random numbers an initial list of 950 students will be selected across the four schools for possible inclusion into the study. Selection will be done separately for each school; each school will be taken as a cluster. The list of selected students will therefore be compiled and will be given serial numbers based on schools. Random allocation of schools (clusters) to groups will be done after baseline data collections.

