**3.10 Training**

There will be two clinicians who will be involve in this study with specialty in public health. Also included will be twelve qualified health staff with Master’s degree qualification, and a physical education health instructor (with Diploma in Physical Education) who will implement the physical activity module of the intervention. All these staff are with the Kintampo Health Research Centre (Ghana Health Service). Clinicians, health staff, and PE health instructor will be selected if they had been involved previously in any of the Ghana Health Service field research. Health staff will be trained by the researcher and clinicians to take anthropometry (body weight and height) and blood pressure (diastolic and systolic BP) measurements. Health staffs (six) who will be involve in the baseline measurements will not take part in the post intervention measurements. Another set of six health staff will do the post intervention measurements to avoid observers’ bias. The objectives of the study will be explained to staff involved in the study. A week’s training will be organized for health staff on anthropometric and blood pressure measurements. The training of health staff will among other things to equip them to avoid inter and intra observer measurements biases.

The study has the involvement of school authorities. A week’s training will be organized for PE and other teachers in the intervention schools by the research team (researcher, clinicians, PE health instructor, and health staff). This will be done to ensure sustainability after the intervention to train new students. The study protocol including all measurements will be reviewed with the clinicians, health staff, physical education health instructor, and teachers before the commencement of the study.

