**SECTIONS 9 AND 10: ANTHROPOMETRIC AND BLOOD PRESSURE MEASUREMENTS TO BE TAKEN BY**

|  |  | **.** |  |
| --- | --- | --- | --- |

|  |  |  | **.** |  |
| --- | --- | --- | --- | --- |

| **FACILITATORS**  **99. Weight (kg)** |  |  |  |  | **WEIGHT** |
| --- | --- | --- | --- | --- | --- |
| **100. Height (cm)** |  |  |  |  | **HEIGHT** |
| **1ST READING** |  |  |  |  |  |
| **101a. Systolic (mmHg)** |  |  |  |  | **SYSTOLIC1** |
| **102a. Diastolic (mmHg)** |  |  |  |  | **DIASTOL1** |
| PLEASE WAIT FOR MEASUREMENT | ONE | MINUTE | BEFORE | TAKING | THE SECOND |
| **2ND READING** |  |  |  |  |  |
| **101b. Systolic (mmHg)** |  |  |  |  | **SYSTOLIC2** |
| **102b. Diastolic (mmHg)** |  |  |  |  | **DIASTOL2** |

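### The declared blinding covers only the baseline measurers, who work before allocation; the six staff who measure at six months are not declared blind

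*Protocol*

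**What the plan says.** The abstract and Section 3.2 describe the trial as single-blind, and Section 3.8 repeats it: "This study is single-blinded". That section names one blinded group, the health staff who measure anthropometry and blood pressure, who "will be blinded to participants groups and will not take anthropometry and blood pressure measurements at the post-test intervention". It then says that the researchers and the physical education health instructor "will not be blinded as such".

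On timing, Section 3.5.2 states: "Random allocation of schools (clusters) to groups will be done after baseline data collections". Section 3.7 says of the assignment of schools: "It will however be performed after baseline data has been collected".

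On staffing, Section 3.10 provides twelve health staff. Six measure at baseline and are barred from the follow-up measurements. For follow-up, "Another set of six health staff will do the post intervention measurements", with avoidance of observer bias as the reason. Section 3.11 repeats that the follow-up measurers are people who did not measure at baseline. Section 3.10 also sets up a week of training for teachers in the intervention schools, given by the "research team (researcher, clinicians, PE health instructor, and health staff"), and does not say which of the twelve health staff are meant.

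**The concern.** A single-blind label tells readers that someone whose knowledge of the group could bias the results is kept unaware of it. Here the one group declared unaware finishes its work before any group exists. The people whose knowledge could matter, those who take weight, height and blood pressure at six months, are covered only by being a different team.

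A fresh team cannot recall a student's baseline reading. That does not conceal which schools received the programme. At stake are the four staff-measured secondary outcomes at the only follow-up, and the accuracy of a design claim that will be carried into the trial report.

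**Working it through.** No arithmetic beyond counting is needed. The check sets timeline, staff roles and outcome sources side by side.

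**Staff count.** 6 baseline measurers + 6 follow-up measurers = 12, which agrees with Section 3.10. The two sets do not overlap.

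**Timeline and declared blinding.**

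| Step | Who measures | Do groups exist yet? | Declared blind? |
|---|---|---|---|
| Baseline measurement | First six health staff (3.10) | No (3.5.2, 3.7) | Yes, by the wording of 3.8 |
| Allocation of schools | – | Created here | – |
| Six-month measurement | Second six health staff (3.10, 3.11) | Yes | Not stated in 3.8, 3.10 or 3.11 |

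In Section 3.8 one subject carries both statements: the staff are blinded, and they do not measure at post-test. The only staff who meet the second condition are the baseline six. Their blindness follows from the timing alone and needs no procedure.

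Section 3.7 also speaks of assignment on the day participants are selected. Its next sentence places it after baseline, and Section 3.5.2 and the abstract agree, so this does not change the order.

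**Coverage by outcome at six months (Section 3.15.2).**

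- Secondary outcomes: body weight, BMI, diastolic and systolic pressure. All are measured by the second six. Covered by declared blinding: 0 of 4.
- Primary outcomes: knowledge, motivation, behavioural skills, physical activity, smoking, alcohol and diet. All come from the student-completed questionnaire (3.12.1, 3.12.2). Students are not said to be blind, and the programme they attend is overt. Covered by declared blinding: 0 of 7. Blinding the measurers could not change this.

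**Routes by which follow-up measurers might learn the allocation.** Section 3.10 places health staff, unspecified, in the team that trains teachers in the intervention schools, and does not exclude the second six. There are four schools in all (3.2), so taking part in training at a school reveals that school's arm. Section 3.7.3 has the allocation announced to school representatives, and no procedure keeps it from measurers who visit later.

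**The case against.** The strongest reply is that this is a drafting slip. The start of the sentence in Section 3.8 is general: staff who take the measurements are blinded. The section lists only the researchers and the instructor as unblinded, and Section 3.10 gives observer bias as the reason for a fresh follow-up team. The sponsor may well have meant all twelve measurers to be blind and merged two sentences into one. This is plausible. It does not remove the point, because the sentence then names the wrong set and neither Section 3.10 nor Section 3.11 supplies the missing statement.

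The second reply is that the room for observer bias is small. Blood pressure is read by an automated monitor, as the average of two readings after five minutes seated (3.12.4). Weight comes from a digital scale (3.12.3), instruments are calibrated daily (3.13.4) and staff are trained to reduce observer variability (3.10, 3.13.5). This stands as mitigation. Staff still seat the student, time the readings and record the values, and none of these measures is blinding to group.

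A reader might infer more than the text supports:

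- *That the follow-up measurers deliver the programme or will know the allocation.* Section 3.14 gives delivery to the researcher and the physical education instructor. The health staff's part is in training teachers, which Section 3.10 justifies as sustainability after the intervention, and the baseline six may be the ones meant. The text shows only that the follow-up six are not excluded.
- *That the form in Appendix A hands measurement to unblinded staff.* The heading of its Sections 9 and 10 ("BLOOD PRESSURE MEASUREMENTS TO BE TAKEN BY") continues with the word facilitators. Sections 3.10, 3.11, 3.12.1, 3.12.3 and 3.12.4 all give measurement to health staff, so this is loose form wording.
- *That unblinded measurers influence the questionnaire.* Section 3.12.2 calls it assisted, but no section says who assists.
- *That the bias can be put in mmHg.* The protocol gives no figure for observer error. The pooled blood pressure effects in Section 2.6.6 come from a cited meta-analysis of childhood obesity prevention and are not this trial's stated target.

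**Conclusion.** The point holds as a gap between the label and what the protocol provides. As written, the declared blinding protects none of the four secondary outcomes at follow-up, and the seven primary outcomes lie beyond the reach of assessor blinding. This rests on the literal wording of Section 3.8, on allocation after baseline, and on the absence of any statement that the six-month measurers are blind.

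The consequence is moderate. The measured outcomes are secondary, the devices limit observer bias, and no size of bias can be derived from the documents. The correction should still be made, because the single-blind claim is unsupported where it would matter and the remedy is cheap.

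**What to change.** 1. **Section 3.8:** state that the six post-intervention measurers are the staff blinded to school allocation, and say how this will be kept at the school visits, given that school representatives are told the allocation.
2. **Section 3.10:** restrict teacher training, and any other contact with the intervention programme, to the baseline six, the clinicians, the researcher and the physical education instructor. The baseline six have finished measuring by then.
3. **Section 3.8:** state that students, and therefore all questionnaire outcomes, are unblinded.
4. **If blinding of the follow-up measurers cannot be kept at the visits:** drop the single-blind label from the abstract and from Sections 3.2 and 3.8.
5. **Appendix A, Sections 9 and 10:** replace facilitators with health staff. This is a wording correction only.

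The cost is a reassignment of duties among the twelve staff already planned, plus the text changes. No extra staff are needed.
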